#### Participant eligibility

2.2.1.

Inclusion criteria include: 1) two self-reported heavy drinking episodes (>4 standard drinks for male assigned at birth, >3 standard drinks for female assigned at birth) or ≥14 standard drinks in the last 14 days at the time of screening; 2) a PEth level that is ≥20 ng/mL at study enrollment; 3) diagnosis of a current AUD as assessed by the Structured Clinical Interview for DSM-5 (SCID) [10]; 4) 18+ years of age; 5) residing in the contiguous USA; 6) fluent in English; 7) access to reliable internet for videoconferencing. Ineligibility criteria include: 1) current SCID diagnosis of a severe drug use disorder, excluding cannabis; 2) receiving other AUD treatment at study enrollment; 3) inability to provide informed consent based on the San Diego Brief Assessment of Capacity to Consent; 4) history of alcohol withdrawal-related seizures or alcohol-related hospitalization in the prior 12 months; or 5) psychiatrically or medically unsafe to participate, per the principal investigator. Should a participant enroll in another AUD treatment after randomization, they will remain in the study.

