#### Randomization procedures

2.2.2.

Eligible participants will be assigned to study arms based on permuted block randomization in REDCap that is stratified by sex (male, female, other, prefer not to say) and PEth levels at the study enrollment visit (<200 ng/mL or ≥200 ng/mL). PEth ≥200 ng/mL equates to regular excessive drinking in the prior two to four weeks [11,12]. Participants will be informed of their treatment condition at the randomization visit, one week after enrollment (see Fig. 1).

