PEth 16:0/18:1 levels will be assessed using a modified method for high-performance liquid chromatography with tandem mass spectrometry [25,26]. All reagents will be purchased from Thermo Fisher Scientific and Sigma Chemical (Fisher Scientific, Waltham, MA). PEth 16:0/18:1 analytical standard will be purchased from Cerilliant (Round Rock, TX). Deuterated PEth (16,0/18,1-*d*5, Echelon Biosciences, Salt Lake, UT) will serve as the internal standard. PEth calibrator (0–2000 ng/mL) and control samples will have a volume of 40 μL. Two plugs from each TASSO-M20 device will be analyzed. Each sample, excluding the blank control, will be spiked with 10 μL of the 0.1 μg/mL deuterated PEth, final concentration 25 ng/mL. PEth will be extracted from the calibrator, control, and experimental samples by the addition of isopropanol (1 mL) with vortexing (1 min), shaking at high speed (45 min, Eberbach Shaker), sonication using 5 second bursts (Q-Sonica, 10% max), and centrifugation at 3,200 g at 4°C (30 min). The clear supernatants will be transferred to new tubes and evaporated to residue with a gentle stream of nitrogen at 30 °C. The residues will be dissolved in 100 μL of a 1:1 resuspension solution of mobile phase A (40,60, 2 mM ammonium acetate,acetonitrile) and mobile phase B (isopropanol) and then transferred to 1.5 mL snap-cap polypropylene microcentrifuge tubes and centrifuged for 10 min (3,200 *g*) at 4°C. The eluted samples will be transferred to 300 μL polypropylene autosampler vials and then 10 μL will be injected into the HPLC/MS/MS system. The ratio of peak areas of PEth 16:0/18:1 to that of d5-PEth 16:0/18:1 of the unknown samples will be compared against a linear regression of ratios of calibrators from 0 to 4,000 ng/mL.

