### Preliminary analyses

3.1.

Our data and supporting documents will be submitted to the National Institute on Alcohol Abuse and Alcoholism’s National Data Archive (NDA) and will be available within three years of completion of the study. Groups will be compared for differences in demographics and pre-treatment alcohol use. Means and standard deviations will characterize continuous variables, and percentages and frequencies characterize categorical variables. We will assess the impact of sex as a biological variable. Our alpha threshold for statistical significance will be 0.05.

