### Treatment efficacy

3.2.

We will follow an intention-to-treat approach to provide unbiased group comparisons. Treatment efficacy will be assessed per our primary outcome, PEth-defined abstinence. In the Starting Phase, abstinence will be defined as a week-over-week decrease in PEth levels (yes/no). During the Sustaining Phase and Follow-up Phase, abstinence will be defined as PEth <20 ng/mL (yes/no). Separate generalized estimating equations (GEE) with logit link functions will be used to assess abstinence during treatment (11 assessments across 26 weeks) and follow-up (4 assessments across 52 weeks). The frequency of PEth-defined excessive drinking (≥200 ng/mL; yes/no) will also be analyzed with GEE. GEEs with appropriate link functions will also assess additional outcomes for the longest duration of PEth-defined abstinence, uEtG results (positive/negative), self-reported days of drinking, self-reported drinks per day, and alcohol-associated harms (cigarette smoking, drug use, utilization of costly medical care). All GEE models will include effects for groups, biological sex, time, and the group-by-time interaction. Statistically significant group-by-time interactions will be evaluated with Bonferroni corrected post hoc tests.

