### Power

3.5.

Our sample size (*n* = 200) is based on statistical power calculations with the primary outcome of detecting group differences in PEth-assessed alcohol abstinence across 11 assessments during treatment and 4 assessments in follow-up. Our missing data techniques will recapture some power lost due to attrition, but we take a conservative approach to ensure adequate power by basing power calculations on a sample size reduced by 25% (*n* = 150). Our pilot study found an increase in abstinence of 43% in the CM group compared to 0% in the Control group. Using methods previously described [45], this effect would result in >99% power with *n* = 150 when comparing abstinence among groups in treatment (G*Power software). While this effect is promising, CM meta-analyses and large RCTs consistently demonstrate odds ratios (ORs) as effect sizes ranging from 1.7 to 4.5 for increasing substance use abstinence [23,46–51]. In addition, CBT4CBT, which all participants will receive, has an effect size on substance use ranging from *d* = 0.11–0.37. These are modest and consistent with CBT interventions that are commonly paired with CM in past trials where CM demonstrated superiority to CBT [47,49,52]. Based on our pilot study, we expect an effect size no smaller than OR = 1.7, which accounts for the underlying effect of CBT in both groups. In the treatment and follow-up period, at a sample size of *n* = 150, we will have at least 80% power to detect a modest effect size of OR = 1.34.

For the secondary aim of reducing the frequency of PEth-defined excessive drinking, our group has consistently found secondary improvements in the odds of substance-related harms to be OR = 1.80 or larger. Assuming a sample size of n = 150, we estimate at least 80% power to detect an OR = 1.80 for reduction in PEth-defined excessive drinking during treatment or the follow-up period.

For analyses of the ANA, our proposed sample size of n = 150 will provide at least 80% power to identify an OR = 1.44 when there are as many as 10 predictors being modeled. This OR corresponds to a small but clinically meaningful change predicted by demographics, our ANA variables, and in-treatment PEth-defined abstinence.

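### The PEth efficacy models use only yes/no outcomes and leave out enrollment PEth, so they give up follow-up precision that data already collected could supply

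*Protocol article*

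**What the plan says.** The article describes a quantitative assay in section 2.5.1: "PEth 16:0/18:1 levels will be assessed using a modified method for high-performance liquid chromatography with tandem mass spectrometry", read against calibrators up to 4,000 ng/mL. Section 2.4 has blood collected at each visit. Everyone randomized has an enrollment value, because section 2.2.1 requires "a PEth level that is ≥20 ng/mL at study enrollment". Section 2.2.2 stratifies randomization by sex and by "PEth levels at the study enrollment visit (<200 ng/mL or ≥200 ng/mL".

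Section 3.2 then defines the PEth outcomes as binary. The primary is abstinence: a week-over-week decrease in the Starting Phase, and <20 ng/mL in the Sustaining Phase and in follow-up. For the secondary, "The frequency of PEth-defined excessive drinking (≥200 ng/mL; yes/no) will also be analyzed with GEE". The other PEth outcome, longest duration of abstinence, is built from the same yes/no definition. All GEE models are given the same terms: group, biological sex, time and group-by-time. Enrollment PEth is not among them.

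For the secondary outcome, section 3.5 states, at n = 150: "we estimate at least 80% power to detect an OR = 1.80 for reduction in PEth-defined excessive drinking during treatment or the follow-up period". It gives neither a control rate nor a within-person correlation.

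**The concern.** Two sources of information are collected and then left out of the efficacy models.

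The first is enrollment PEth. It was judged important enough to stratify on and is likely to predict later PEth strongly. Leaving a strong predictor out of the model gives up precision, and leaving out a stratification factor usually makes the reported standard errors too large.

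The second is the PEth level itself. In follow-up, a participant who falls from 150 to 30 ng/mL has not reached <20 and was never at ≥200, so no PEth outcome registers the change. A fall from 900 to 220 is not registered either. Entrants at 20-199 ng/mL start in the favourable category of the secondary outcome and can influence it only by rising, or not rising, to 200.

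At stake is the secondary aim over the 12-month follow-up, which has only four assessments. A real reduction in drinking could be reported as non-significant because of how the data were modelled.

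**Working it through.** **Inputs from the article.** n = 150 after the 25% allowance; 4 follow-up assessments; OR 1.80; alpha 0.05.

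**Assumptions not in the article.** 1:1 allocation (75 per arm), a two-sided test, the control rate of PEth ≥200, the within-person correlation, and the spread of PEth.

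**Step 1: the plan's own power figure.** Effective n per arm = 75m / (1 + (m - 1)ρ), entered in the two-proportion formula: power = Φ[(d - 1.96·se0) / se1].
- With a control rate of 0.5, the odds become 1/1.80 = 0.556, so the CM rate is 0.357 and d = 0.143.
- With m = 4 and ρ = 0.2: effective n = 300/1.6 = 187.5, se0 = 0.0511, se1 = 0.0506. Power = Φ[(0.1429 - 0.1002)/0.0506] = 80%.
- With ρ = 0.5: effective n = 300/2.5 = 120, se0 = 0.0639, se1 = 0.0632. Power = Φ[(0.1429 - 0.1252)/0.0632] = 61%.
- Over control rates 0.2-0.6, power at ρ = 0.5 is 38-62%. The stated 80% needs ρ of at most about 0.06 (control rate 0.3), 0.15 (0.4) or 0.20-0.21 (0.5-0.6), and is not reached at 0.2.

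So the figure is reachable in follow-up only with low correlation. It cannot be confirmed or refuted from the article, but it leaves little precision to spare.

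**Step 2: cost of the cut, without covariates.** Take one normal shift in log PEth that produces OR 1.80 at the cut. At control rate 0.5 the shift is 0.366 SD. A correlation of 0.5 on the log scale corresponds to about 0.33 on the yes/no scale.
- Cut: effective n = 300/(1 + 3 × 0.33) ≈ 151; power 71%.
- Log PEth: effective n = 120; power = Φ(0.366·√60 - 1.96) = Φ(0.875) = 81%.

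At control rate 0.3 the pair is 60% and 76%; at 0.2 it is 48% and 71%. Over correlations 0.3-0.8 the difference is about 9 to 24 points.

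**Step 3: the covariate and the scale, separated by simulation.** Enrollment log PEth is normal with SD 1.1, truncated at 20 ng/mL; 40-70% of entrants are ≥200; control follow-up prevalence is 10 points below entry; correlation is 0.5-0.7; values are floored at 8 or 20 ng/mL. Per-participant means over the 4 visits are compared between arms with a robust-variance linear model. The effect is calibrated to OR 1.80 at the cut.

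One setting (55% ≥200, correlation 0.5, floor 8, uniform fall):

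| Analysis | Power |
|---|---|
| Cut | 69.5% |
| Cut + enrollment log PEth | 83.0% |
| Log PEth | 80.3% |
| Log PEth + enrollment log PEth | 95.1% |

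Of the 95.1 - 69.5 = 25.6 points, the covariate alone gives 83.0 - 69.5 = 13.5, and the change of scale the other 12.1.

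Across settings:
- Uniform fall, unadjusted: cut 52-72%, log PEth 70-80%.
- Uniform fall, both adjusted: cut 73-90%, log PEth 92-99%.
- Adding the covariate to the cut: about +13 to +29 points with a uniform fall, and about +9 to +23 under the other patterns (a fraction becoming abstinent, or an effect only in entrants ≥200).
- Log PEth instead of the cut, both adjusted: about +8 to +20 with a uniform fall, and about -2 to +12 if the effect is confined to entrants ≥200.

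Repeating the simulation moved the ends of these ranges by up to about two points.

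**The case against.** The strongest reply is that 200 ng/mL defines the question. Section 2.2.2 equates it with regular excessive drinking, and the introduction names absence of such drinking in the primary aim. A reader might infer that log PEth should replace the cut as the tested outcome. The article does not support that, because its stated aim would then go untested. The two scales can also disagree. In a constructed scenario where CM moved only entrants below 200 to the floor, and only at visits that would have been below 200 anyway, the ≥200 rates were identical by arm, yet adjusted log PEth was significant in 35-99% of trials. That signal belongs to the primary outcome. This objection stands and determines the fix.

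A reader might also infer that entrants at 20-199 ng/mL can hardly show benefit. That is too strong. CM can keep them from rising to 200, and reaching <20 is a primary success. Under one set of assumptions the cut alone had 28-53% power within this stratum, against 46-83% for log PEth. During treatment, week-over-week decreases count in the Starting Phase, and section 3.2 also analyses self-reported drinking days and drinks per day. Graded change is therefore not invisible everywhere; the gap is in the biomarker analyses of follow-up.

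Finally, the full protocol or a separate analysis plan may add continuous or adjusted analyses. For the supportive analysis that is a fair caution. The covariate is different: the article lists the terms for all GEE models, so this is a stated choice.

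**Conclusion.** The point holds as a loss of efficiency, not as an error or a bias. Section 3.2 leaves out the enrollment value it stratifies on and uses no concentration in any efficacy analysis. The more dependable gain is the covariate, which keeps the aim and outcome intact and helped under every effect pattern tried. The gain from the log scale is real under a uniform fall but may vanish if only heavier drinkers benefit.

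A reader might take a fixed loss, such as 10 to 20 points of power, as established. It is not. The control rate, correlation, PEth spread and effect pattern are all assumed, and the simulation compares visit-averaged means with a linear model rather than fitting the planned logit GEE. The primary outcome definition is unaffected. The change should be made but is not critical.

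**What to change.** In section 3.2:
1. Keep the ≥200 ng/mL GEE as the tested secondary outcome.
2. Add enrollment log PEth as a covariate to the PEth efficacy models or, at the least, the <200/≥200 stratum, which would carry less information.
3. Pre-specify a supportive analysis of log PEth concentration, adjusted for enrollment log PEth, in follow-up and at visit weeks common to both arms during treatment. The restriction matters because CM participants who drink return to weekly sampling. Report a ratio of geometric means, assign one fixed value to results below the quantification limit, and add a rank-based check.

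The cost is revised model wording and one extra model per period, with no new samples, visits or participants. There are three downsides. The log PEth result partly overlaps with the primary abstinence outcome. It also depends on the value substituted below the quantification limit, in a trial designed to push results there. And with a logit link, the adjusted odds ratio is conditional on enrollment PEth, so it is not on the same scale as an unadjusted OR of 1.80; the section 3.5 power statement should say which is meant.

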#### Self-reported alcohol use

2.5.3.

Self-reported daily alcohol use will be assessed at each visit using the Alcohol Timeline Followback (ATLFB) [27]. This information will reflect the thirty days prior to the enrollment visit, as well as “since the last visit” at each subsequent visit. Additionally, we will record hours since the last drinking episode and the number of drinks at the last drinking episode.

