#### Economic measures

2.5.6.

The NMOS form will be used to measure resource utilization needed to inform the state-policymaker and societal perspectives, including criminal-legal, social safety-net, labor/school productivity, travel time to medical care, and caregiver time. This form utilizes time-anchoring methodology to assess participant resource use over the 30 days prior to the enrollment visit, and then “since your last visit” at each subsequent administration. The Drug Abuse Treatment Cost Analysis Program instrument will be used to guide the microcosting analysis (see 3.3.2) [31].

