**Fig. 2. F2:**
[figure not shown]
CM Treatment Schedule: CM participants will remain in the Starting Phase for the first four weeks of treatment or until their PEth levels indicate abstinence (<20 ng/mL). They will then transition to the Sustaining Phase of treatment, where they are reinforced for maintaining PEth levels below 20 ng/mL. Should a participant in the Sustaining Phase have a PEth level ≥20 ng/mL, they will return to weekly visits (i.e., Starting Phase). Once PEth levels are again <20 ng/mL, participants will return to monthly visits in the Sustaining Phase. Regardless of how many times a participant returns to the Starting Phase, the treatment duration will remain 26 weeks.

**Table 1 T1:** Study measures and data collection schedule: See methods for a description of each measure. Acronyms included are phosphatidylethanol (PEth), urine ethyl glucuronide (uEtG), Non-study Medical and Other Services (NMOS), Drug Abuse Treatment Cost Analysis Program (DATCAP), Client Satisfaction Questionnaire (CSQ-8), and the Sweating, Hallucinations, Orientation, Tremor scale (SHOT).

Measure	Enrolment Visit	Every Visit	Treatment Visits Week 4, 8, 12, 16, 20, 26	Follow-Up Visits Week 30, 38, 52, 78
Eligibility Criteria	✓			
Demographics	✓			
PEth-Defined Abstinence <20 ng/mL	✓	✓		
PEth-Defined Excessive Drinking ≥ 200 ng/mL	✓	✓		
uEtG-Defined Recent Drinking: ≥ 300 ng/mL	✓	✓		
Self-Reported Alcohol Timeline Followback	✓	✓		
Self-Reported Cigarette Timeline Followback	✓	✓		
Nicotine dependence: Fagerstrom	✓		✓	✓
Drug Use: 5-Panel Cup	✓	✓		
ANA Model: Questionnaire	✓	✓		
ANA Model: TestMyBrain	✓			
Healthcare Utilization: NMOS	✓		✓	✓
Intervention cost: DATCAP	✓			
Attrition: Percent missed visits		✓		
Client Satisfaction: CSQ-8			Weeks 4, 26	
Alcohol withdrawal: SHOT	✓	✓		
Adverse Events	✓	✓		

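### The GEE term list for the non-PEth outcomes omits each outcome's enrollment value, although it is collected, so group contrasts are less precise than they need be

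*Protocol article*

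**What the plan says.** Section 3.2 (Treatment efficacy) sets the model terms: "All GEE models will include effects for groups, biological sex, time, and the group-by-time interaction". Besides the PEth outcomes, the GEEs cover uEtG results and "self-reported days of drinking, self-reported drinks per day, and alcohol-associated harms (cigarette smoking, drug use, utilization of costly medical care".

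Each of these has a value at enrollment:

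- **Drinking:** the Alcohol Timeline Followback (section 2.5.3). "This information will reflect the thirty days prior to the enrollment visit, as well as “since the last visit” at each subsequent visit".
- **Medical care:** the NMOS form (section 2.5.6) is used to "assess participant resource use over the 30 days prior to the enrollment visit", and Table 1 ticks it at enrollment.
- **Cigarettes, uEtG and drug use:** Table 1 ticks the enrollment visit for the row "Self-Reported Cigarette Timeline Followback" and for the uEtG and drug-cup rows.

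Section 3.1 adds a baseline comparison: "Groups will be compared for differences in demographics and pre-treatment alcohol use". It does not say that any compared value is carried into a model. Section 2.2.2 stratifies randomization by sex and by enrollment PEth (below 200, or 200 ng/mL and above). Adjustment for potential confounders appears only in the economic effectiveness models of section 3.3.2.

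**The concern.** Drinking, smoking and use of care can be expected to differ widely between people and to persist within a person. Eligibility sets a floor on recent drinking but no ceiling, and requires neither smoking nor use of care. If the enrollment value is left out, the part of the between-person spread that it could explain stays in the error of the group contrast.

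Stratification does not replace it. The PEth stratum may partly balance self-reported drinking, but it does not address cigarettes or medical care, and it is not among the model terms either.

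At stake is the power to show an effect on self-reported drinking and on alcohol-associated harms, one of the additional aims in the Introduction. Because the article states the terms for all GEE models, an analysis plan that follows the sentence as written would carry the omission forward.

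**Working it through.** **No figure of the plan to reproduce.** Section 3.5 gives no power for the self-reported drinking, cigarette, drug-use, uEtG or medical-care outcomes, and no correlation between enrollment and later values. The calculation therefore starts from a contrast with 80% unadjusted power and varies the correlation.

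**Inputs**
- n = 150 (section 3.5, 200 less 25%), taken as 75 per arm.
- Alpha 0.05 (section 3.1), taken as two-sided.
- Correlation r between the enrollment value and each later value: assumed 0.3, 0.5 and 0.7.
- Number of visits k: 4 (follow-up visits), 6 (NMOS treatment visits in Table 1: Weeks 4, 8, 12, 16, 20 and 26) and 11 (treatment assessments).
- Outcome treated as roughly continuous.

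**Single measure.** Adjustment multiplies the variance by 1 − r². Power = Φ((0.842 + 1.960)/√(1 − r²) − 1.960).

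| r | 1 − r² | Argument of Φ | Adjusted power |
|---|---|---|---|
| 0.3 | 0.91 | 0.977 | 83.6% |
| 0.5 | 0.75 | 1.275 | 89.9% |
| 0.7 | 0.51 | 1.963 | 97.5% |

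**Mean of k visits, equal correlation r throughout.** The unadjusted variance factor is (1 + (k − 1)r)/k. With the enrollment value as covariate it is that quantity minus r². For k = 6 and r = 0.5: (1 + 2.5)/6 = 0.583; 0.583 − 0.25 = 0.333; ratio 0.571. So about 0.571 × 150 = 86 adjusted participants give the precision of 150 unadjusted.

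| k | r = 0.3: ratio, power | r = 0.5: ratio, power | r = 0.7: ratio, power |
|---|---|---|---|
| 4 | 0.81, 88% | 0.60, 95% | 0.37, >99% |
| 6 | 0.78, 89% | 0.57, 96% | 0.35, >99% |
| 11 | 0.75, 90% | 0.54, 97% | 0.33, >99% |

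Simulated exchangeable GEEs (k = 6, 300 trials per setting) agree. At r = 0.5 the standard error of the group effect falls from 0.124 to 0.093 and power rises from 0.80 to 0.96. At r = 0.7 the standard error falls from 0.140 to 0.083 and power rises from 0.83 to 1.00.

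**Chance imbalance, the same variance seen another way.** With 75 per arm the baseline difference has a standard deviation of √(2/75) = 0.163 outcome SDs, so its 95% range is ±0.32. A fraction r of it carries into the unadjusted contrast: at the edge of that range, 0.10 SD for r = 0.3 and 0.22 SD for r = 0.7.

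**Group-by-time test.** Balanced 11-visit data (n = 150, r = 0.5, identity link) were fitted with and without the enrollment covariate. The interaction standard error was identical: 0.010745 both ways for linear time, and 0.163158 both ways for the last visit with categorical time. A covariate that is constant within a person does not alter a within-person contrast there. The gains above therefore belong to the group contrast, overall or at a visit.

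**The case against.** The strongest reply has four parts.

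**The enrollment value might already be in the models.** The statement on visit counts, "abstinence during treatment (11 assessments across 26 weeks) and follow-up (4 assessments across 52 weeks", is written for the abstinence GEEs. The visit set for the other outcomes is not given, and NMOS cannot follow the 11-visit schedule. A reader might infer that enrollment is certainly excluded as a repeated measure from every model. The text does not establish that. It is silent, and if enrollment were a time level, the group-by-time term would use it. This part stands, and the fix allows for it.

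**A condensed article leaves such detail to the analysis plan, and listing terms does not mean no others.** This has some force. But the sentence covers all GEE models and names a covariate, sex, while omitting one that is already collected. Adding it is a specific improvement to a stated choice.

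**The plan is valid as it stands.** A reader might infer that chance imbalance biases the estimate. It does not: randomization keeps the contrast unbiased on average, and the standard error already allows for imbalance. Lost power and uncorrected imbalance are largely one loss and should not be counted twice.

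**The gain is assumed and partial.** Entry requires recent heavy drinking, which narrows the baseline range, and both arms are treated to change drinking, so the correlation may be modest. Use of care is measured over unequal windows, and the urine results are binary. The only follow-up testing that section 3.2 describes depends on the interaction, which gains little or nothing. All of this limits the size. None of it makes the unadjusted contrast the better choice.

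**Conclusion.** The point holds as a nearly costless gain in precision for additional outcomes, not as an error that invalidates the analysis. The stated terms do not include the outcome's enrollment value, and nothing elsewhere in the article supplies it. For a roughly continuous outcome at n = 150, 80% unadjusted power for the group contrast becomes about 84% to 97.5% for a single measure over r = 0.3 to 0.7, and about 88% to over 99% when 4 to 11 visits are averaged. These figures rest on assumed correlations, equal correlation across visits and no model term that already uses enrollment. Medical-care counts and urine results may gain less.

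A reader might extend the point to the primary outcome. That does not follow: entry requires PEth ≥20 ng/mL, so no participant is PEth-abstinent at enrollment and there is no baseline abstinence status to adjust for. Nor does the harms aim depend on these GEEs alone, since section 3.3.2 also compares costs, including medical costs, between arms.

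**What to change.** In section 3.2, state that each GEE for a non-PEth repeated outcome named there and measured at enrollment also includes that outcome's enrollment value as a prespecified covariate, whatever the section 3.1 comparison shows. Specify its form:

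- **Timeline Followback and NMOS measures:** a rate per day, because the enrollment window is 30 days and later windows run from the previous visit. A plain log is undefined for participants with no cigarettes or no care use, so where zeros occur use log(rate + constant), or an any-use indicator plus the rate.
- **uEtG and drug cup:** the enrollment positive or negative result.

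If enrollment is instead meant to be a time level in these models, say so and do not also add it as a covariate.

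The cost is a few sentences before unblinded analysis and one or two extra parameters per model, with no new data, visits or participants. In logit models the group effect becomes conditional on the enrollment value, which should be stated when results are reported.

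### Randomization is stratified by enrollment PEth (below or at least 200 ng/mL), but the term list for every GEE leaves PEth out, which makes the test conservative and gives away power

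*Protocol article*

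**What the plan says.** Section 2.2.2 (Randomization procedures) says that assignment is "stratified by sex (male, female, other, prefer not to say) and PEth levels at the study enrollment visit (<200 ng/mL or ≥200 ng/mL"). It also explains why the cut-off was chosen: "PEth ≥200 ng/mL equates to regular excessive drinking in the prior two to four weeks".

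Section 3.2 (Treatment efficacy) lists the model terms: "All GEE models will include effects for groups, biological sex, time, and the group-by-time interaction". The sentence covers every GEE, so it applies to the primary outcome in both the treatment and the follow-up model, and to the secondary outcome.

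The outcomes come from the same assay as the stratum:
- In the Starting Phase the primary outcome is a change: "In the Starting Phase, abstinence will be defined as a week-over-week decrease in PEth levels (yes/no").
- After that it is a level: "During the Sustaining Phase and Follow-up Phase, abstinence will be defined as PEth <20 ng/mL (yes/no").
- The secondary outcome uses the stratum's own cut-off: "The frequency of PEth-defined excessive drinking (≥200 ng/mL; yes/no) will also be analyzed with GEE".

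Nothing elsewhere puts enrollment PEth back into these models. Section 3.1 only compares the groups on pre-treatment alcohol use. Section 3.3.1 concerns predictors for a different aim. The 11 treatment and 4 follow-up assessments all come after randomization, so the enrollment value does not enter as a repeated outcome either.

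**The concern.** Stratified blocks balance the arms on the PEth stratum. The group difference therefore carries almost no variation from that source. A model without the stratum still counts that variation as noise and reports a standard error as if it were present. The test then rejects less often than 5% when there is no effect, and less often than it could when there is one.

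Enrollment PEth is the stronger candidate of the two stratification factors. It is the baseline of the outcome measure, it is available for everyone because a level of at least 20 ng/mL is an inclusion criterion (Section 2.2.1), and the trial judged it important enough to balance on. A participant who enrolls with a high level has further to fall to get below 20 ng/mL and is more likely to remain at or above 200 ng/mL.

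What is at stake is efficiency. The omission does not bias the intention-to-treat comparison and does not inflate false positives.

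**Working it through.** **Inputs from the article.** The stratification factors and model terms are as above. There are 11 treatment and 4 follow-up assessments (Section 3.2), alpha is 0.05 (Section 3.1), and power is based on n = 150 (Section 3.5). The expected effect is no smaller than an odds ratio of 1.7 (Section 3.5). I assume 75 per arm and a two-sided test, because neither the allocation ratio nor the sidedness is stated.

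**The plan's own figure first.** Section 3.5 claims more than 99% power for 43% v 0% abstinence. With 75 per arm, the pooled proportion is 0.215.
- Null SE = √(2 × 0.215 × 0.785 / 75) = 0.0671
- Alternative SE = √(0.43 × 0.57 / 75) = 0.0572
- z = (0.43 − 1.96 × 0.0671) / 0.0572 = 5.22, so power exceeds 99.99%

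The claim reproduces. That effect is so large that covariates would not matter for it. They matter at the more modest effects that the section goes on to plan for.

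**Is there power to spare?** Section 3.5 also claims 80% power at an odds ratio of 1.34 but gives no base rate or within-person correlation. Take the effective size per arm as 75m / (1 + (m − 1) × ICC), where m is the number of assessments. With m = 11, 80% is reached only at an ICC of about 0.01 or less. With m = 4, power is at most 43% even at an ICC of 0. That is a separate issue, but it shows that the trial cannot easily give power away.

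**Size of the conservatism, by hand.** If the stratum explains a share R² of the between-person variance, the unadjusted z statistic shrinks by √(1 − R²), and null rejection is about 2Φ(−1.96 / √(1 − R²)). Assume half the sample in each stratum, a random-intercept SD of 1.5 on the logit scale, and 11 assessments. For a stratum-outcome odds ratio of 0.25:
- Stratum variance = 0.25 × (ln 0.25)² = 0.480
- Total = 0.480 + 1.5² + (π²/3)/11 = 3.03
- R² = 0.480 / 3.03 = 0.159
- Null rejection = 2Φ(−1.96 / √0.841) = 2Φ(−2.14) = 3.3%

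The same steps give 4.5% at an odds ratio of 0.5, 1.6% at 0.1 and 0.7% at 0.05.

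**Simulation on the same assumptions.** The settings were 4,000 trials per cell, n = 150, blocks of 4 within sex by PEth stratum, and a logit GEE with independence working correlation and robust SE. The group effect was tested at mid-period. Power is for a conditional odds ratio of 1.7. Monte Carlo 95% margins are about ±0.7 points on a 5% null rate and ±1.5 points on power.

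| Assessments | Stratum-outcome OR | Null rejection, no PEth | Null rejection, with stratum | Power, no PEth | Power, with stratum |
|---|---|---|---|---|---|
| 11 | 1 | 5.4% | 5.3% | 48% | 48% |
| 11 | 0.5 | 4.7% | 5.2% | 46% | 48% |
| 11 | 0.25 | 3.4% | 5.5% | 41% | 48% |
| 11 | 0.1 | 1.5% | 5.2% | 29% | 46% |
| 11 | 0.05 | 0.8% | 5.4% | 18% | 45% |
| 4 | 0.25 | 4.1% | 5.4% | 33% | 37% |
| 4 | 0.1 | 2.4% | 5.9% | 24% | 36% |

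The simulated null rates agree with the hand calculation. The power levels depend on the assumed correlation and are not estimates of this trial's power. Only the contrast between the two models bears on the point.

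**A level outcome generated from log PEth.** With 7 visits, 17% v 34% abstinent, an exchangeable GEE and 400 trials per setting, the correlation of enrollment with in-treatment log PEth was varied from 0.42 to 0.86. Power was 87-88% without PEth, 90-93% with the stratum and 90-100% with log enrollment PEth. Null rejection was 2.5-4.2% without PEth and 4.5-5.0% with log PEth.

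**The composite outcome as defined.** Here all 11 visits were simulated, with a week-over-week decrease counted in Weeks 1-4 and a level below 20 ng/mL afterwards (n = 150, 1,000 trials per cell).

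| Assumed correlation | Null rejection, no PEth | Power, no PEth | Power, stratum | Power, log PEth |
|---|---|---|---|---|
| 0.40 | 4.9% | 44% | 46% | 48% |
| 0.65 | 3.3% | 48% | 54% | 57% |
| 0.85 | 2.8% | 44% | 61% | 71% |

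Excessive drinking and the 4-visit follow-up model gained similarly.

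**The case against.** The strongest objection concerns size. Four of the Control group's 11 treatment visits fall in Weeks 1-4, where the primary outcome is a decrease, not a level. Enrollment PEth has less reason to predict that. A simulation of the composite under other assumptions (n = 150, 2,500 trials per cell, a Starting Phase indicator in the model, correlation parameter 0.42, 0.65 and 0.86) found that adding the stratum gained only 0.6, 1.4 and 2.5 points of power. Null rejection without PEth was 4.6%, 4.4% and 2.6%. The same set-up restricted to the 7 later visits gained 2, 6 and 9 points. So the gain for the in-treatment composite can be small, and the 2 to 17 points in the second table above are not guaranteed. It can also be more than small, and the treatment composite is only one of the affected models.

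Other objections stand in part:
- The article does not quantify how strongly enrollment PEth predicts outcome. At a stratum odds ratio of 0.5 the loss is negligible. This is true, and it is why the size is given as a range.
- In the 400-trial runs the Monte Carlo margin is about ±3 points on power and ±2 points on a 4.2% null rate, so that null rate cannot be told apart from 5%. This is also true. The runs of 4,000 trials do not have this weakness.
- With a logit link, adjustment changes the target to a different conditional odds ratio (median 1.48 v 1.44 at a stratum odds ratio of 0.25). This is correct and has to be part of the fix.
- Listing terms to be included does not strictly exclude others, and a fuller protocol or SAP may add PEth. But the sentence speaks for all models and names one stratification factor while leaving out the other. If a fuller document differs, the two need to agree.

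**Conclusion.** The concern holds. The randomization is stratified on enrollment PEth and the stated efficacy models do not carry it. The direction is clear: standard errors too large, null rejection at or below 5%, and power lost, with no bias and no inflation of false positives.

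The size rests on an assumption that the documents do not supply. The loss is negligible if the stratum-outcome odds ratio is near 0.5. It is about 7 points of power at 0.25 and 17 points at 0.1 with 11 assessments, and 4 and 12 points with 4 assessments. On the composite treatment outcome, adding the stratum gained anywhere from under 1 to 17 points, depending on the assumed correlation and how the visits were modelled. The effect is probably largest for excessive drinking, whose cut-off is the stratum's own, and smallest for the Starting Phase decrease. When the stratum did not predict outcome, including it cost nothing (48% v 48%). This should be changed, but it does not threaten the validity of the trial.

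**What to change.** In Section 3.2, add log-transformed enrollment PEth, or at least the stratum split at 200 ng/mL, to the term list for abstinence and excessive drinking, in both the treatment and the follow-up models. State that the reported group odds ratio is conditional on enrollment PEth and sex, so that the target is fixed in advance. Use the same sentence to say how the four sex categories used in randomization map to the biological sex term in the models. Settle this before outcome data are compared by arm, so that the choice of covariates cannot look data-driven.

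The cost is one covariate already measured in everyone, a change of plan wording, and the explicit statement of the target odds ratio. No visit, sample or procedure changes.
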